**4.1.3 Individual Stopping Criteria**

Dosing will be discontinued in an individual participant in case of:

• AST or ALT elevation of ≥ Grade 2 considered to be related to RO7486967.

• Serious and/ or severe, medically significant RO7486967-related AEs.

• Infection with SARS-CoV-2.

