**7.1 DISCONTINUATION OF STUDY TREATMENT**

For data to be collected at the time of treatment discontinuation and follow-up and for any further evaluations that need to be completed see the SoA (Section 1.3).

Reasons for discontinuation of study treatment (or withdrawal from the study) may include, but are not limited to, the following:

• Participant withdrawal of consent at any time.

• Any medical condition that the Investigator or Sponsor determines may jeopardize the participant’s safety if he or she continues in the study.

• Investigator or Sponsor determination that treatment discontinuation is in the best interest of the participant.

• Pregnancy.

• Any event that meets stopping criteria as defined in Section 4.1.3.

If a clinically significant finding is identified (including, but not limited to, changes from baseline in QT interval corrected using Fridericia’s formula [QTcF]) after enrollment, the Investigator or qualified designee will determine if the participant can continue in the study and if any change in participant management is needed. The review of the ECG printed at the time of collection must be documented. Any new clinically relevant finding should be reported as an AE.

Every effort should be made to obtain information on participants who withdraw from the study but have not withdrawn consent. Participants who discontinue study treatment prematurely will have a study completion/early withdrawal visit (see Section 8.8.3),

unless the participant withdrew consent. The primary reason for premature study treatment discontinuation should be documented on the appropriate eCRF. Participants who discontinue study treatment prematurely may be replaced (see Section 7.2).

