**Table 5 Guidelines for Managing Liver Function Test Abnormalities**

| **Abnormality* Action to Be Taken** |
| --- |
| Grade 1 AST or ALT • Continue study treatment  elevation or • Collect a sample for exploratory safety biomarkers  AST/ALT > ULN to  ≤ 3 × ULN • Monitor LFT (i.e., AST, ALT, ALP, TBL) every 3 days until  values resolve to normal or baseline value. |
| Grade 2 AST or ALT • Discontinue study treatment  elevation or • Monitor LFT (i.e., AST, ALT, ALP, TBL) every 48-72 hours  AST/ALT > 3 to ≤ 5 × ULN until values resolve to normal or baseline value.  • Collect a sample for exploratory safety biomarkers  • Events > 5 days duration:  o Obtain hepatology consultation; evaluate etiology. |
| Grade 3 AST or ALT • Discontinue study treatment  elevation or • Monitor LFT (i.e., AST, ALT, ALP, TBL) every 24-48 hours  AST/ALT > 5 to ≤ 20 × ULN until decreasing and then follow every 48-72 hours  • Collect a sample for exploratory safety biomarkers  • Events > 5 days duration:  o Obtain hepatology consultation; evaluate etiology. |
| Grade 4 AST or ALT • Discontinue study treatment elevation or  AST/ALT > 20 × ULN • Follow management guidelines as described for Grade 3  event. |
| AST or ALT ≥ 3 × ULN in • Consider event an AE of special interest (potential Hy’s law combination with total case) and report *immediately, without undue delay* (see bilirubin ≥ 2 × ULN or Appendix 3, Section 6).  clinical jaundice as defined  by Hy’s law • Collect a sample for exploratory safety biomarkers  • Permanently discontinue study treatment.  • Repeat LFT (i.e., AST, ALT, ALP, TBL) every 24-48 hours to confirm the abnormalities and to determine if they are increasing or decreasing and then follow every 48-72 hours.  • Monitor participant closely for clinical signs and symptoms  • Events > 5 days duration:  o Obtain hepatology consultation; evaluate etiology. |

AE = adverse event; ALP = alkaline phosphatase; ALT = alanine transaminase; AST = aspartate transaminase; LFT = liver function test; NCI CTCAE = National Cancer Institute Common Terminology Criteria for Adverse Events; TBL = total bilirubin; ULN = upper limit of normal.

*AE grading based on NCI CTCAE (v5.0).

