**Table 6 Guidelines for Managing Infections**

| **Event Action to Be Taken** |
| --- |
| Grade 1 infection • Continue study treatment.  • Closely monitor the evolution of the event until resolution.  • Treatment as per local guidelines. |
| Grade 2 infection • Confirm infection:  oObtain complete blood count with differential.  o Obtain necessary tests or cultures and identify pathogen (if possible).  o Additional work-ups should be based on clinical suspicion and local standard of care.  • Discontinue study treatment.  • Closely monitor the evolution of the event until resolution.  • Oral intervention indicated (e.g., antibiotic, antifungal, antiviral)  according to local treatment guidelines. |
| Grade 3 and • Confirm infection:  Grade 4 infection o Obtain complete blood count with differential.  o Obtain necessary tests or cultures and identify pathogen (if possible).  o Additional work-ups should be based on clinical suspicion and local standard of care.  • Discontinue study treatment.  • Close monitor the evolution of the event until resolution.  • Intravenous intervention indicated (e.g., antibiotic, antifungal, antiviral) according the local treatment guidelines. |
| Confirmed SARS- • Discontinue study treatment.  CoV-2 infection • Closely monitor the evolution of the event until resolution. (any grade) • Treatment as per local guidelines, depending on severity. |

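### Section 4.1.3 and Tables 5 and 6 give different triggers for stopping study treatment, and nothing says which governs

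*Combined protocol and SAP*

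**What the plan says.** Section 4.1.3 (Individual Stopping Criteria) is worded as mandatory: "Dosing will be discontinued in an individual participant in case of" any of three events. They are:

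- "AST or ALT elevation of ≥ Grade 2 considered to be related to RO7486967"
- "Serious and/ or severe, medically significant RO7486967-related AEs"
- "Infection with SARS-CoV-2"

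Section 8.2.8 (Management of Specific Adverse Events) contains two tables that also say when to stop.

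- **Table 5, liver tests.** The Grade 2 row begins "Grade 2 AST or ALT • Discontinue study treatment" and the next row "Grade 3 AST or ALT • Discontinue study treatment". The Grade 4 row gives the same instruction. None of the three mentions relatedness. Grade 1 continues.
- **Table 6, infections.** The row that opens "Grade 2 infection • Confirm infection" goes on to instruct discontinuation, as does the row for Grades 3 and 4. Neither depends on cause or pathogen. Confirmed SARS-CoV-2 stops treatment at any grade. Other Grade 1 infections continue.

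Section 6.1 sends the reader to Section 7 for discontinuation. Section 7.1 lists, among other reasons, "Any event that meets stopping criteria as defined in Section 4.1.3". It does not mention Section 8.2.8 or either table, but its list is expressly open-ended.

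**The concern.** Liver injury and infection are the first two risks listed in Section 2.3, and Section 8.2.8 is cited there as the place where their management is set out. A site with a Grade 2 ALT rise that the investigator attributes to something else, or with a moderate bacterial infection, finds a stop in the tables and no matching stop in Section 4.1.3. No passage ranks one text above the other.

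For liver tests, the answer under Section 4.1.3 turns on a blinded causality judgement that Table 5 does not ask for. Unrelated verdicts are plausible: Section 6.5.1 lets participants stay on azathioprine, 6-mercaptopurine or methotrexate and take paracetamol, and Appendix 2, Section 3.2, tells investigators to weigh concomitant medication and the disease itself.

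If investigators read the texts differently, like participants are managed differently. This is first a matter of participant safety. It also affects the tabulation of adverse events leading to discontinuation (Table 8), and whether a participant contributes a full Day 5 PK profile and a Day 7 biopsy on schedule. With about 12 active and 6 placebo participants, a single inconsistency is visible in every summary.

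**Working it through.** The plan gives no figure to reproduce, because no hypothesis is tested (Section 9.1) and the sample size rests on feasibility (Section 9.2). The check is a comparison of triggers, followed by the cross-references.

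**1. Triggers side by side**

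| Case | Section 4.1.3 | Table 5 or 6 | Result |
|---|---|---|---|
| AST/ALT Grade 2 or higher, judged related | Stop | Stop | Agree |
| AST/ALT Grade 2 or higher, judged unrelated | No criterion met | Stop | Differ |
| Infection other than SARS-CoV-2, Grade 2, non-serious, related or not | No criterion clearly met | Stop | Differ |
| Infection other than SARS-CoV-2, Grade 3 or 4, judged unrelated | No criterion met | Stop | Differ |
| Infection other than SARS-CoV-2, Grade 3 or 4, related and medically significant | Stop (second bullet) | Stop | Agree |
| SARS-CoV-2 confirmed, any grade | Stop | Stop | Agree |
| AST/ALT Grade 1, or other infection Grade 1 | No specific criterion | Continue | Agree |

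Three of the seven cases differ. In each, the tables stop treatment and Section 4.1.3 is silent. In none does one text say stop and the other say continue.

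**2. Effect of the relatedness condition.** If Table 5 always applies, every elevation of Grade 2 or higher stops treatment and the condition in the first bullet of Section 4.1.3 does nothing. If the condition is meant to do something, it is at odds with Table 5. Both cannot be intended.

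**3. Cross-references.** The route by which a site looks up discontinuation runs from 6.1 to 7.1 to 4.1.3 and does not reach 8.2.8. Section 8.2.8 is cited elsewhere: in Section 2.3 for liver tests and infection, and in Schedule of Activities Table 1 and Section 8.6.1.1, where the subject is when to take exploratory safety samples. None of these says how the tables relate to Section 4.1.3.

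**4. Can the frequency be estimated?** The only related figure is in Section 2.3: 4 of 18 healthy volunteers on repeated dosing of the drug had a mild transaminase increase.

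- 4/18 = 22.2%, exact 95% interval 6.4% to 47.6%.
- If mild there means Grade 1 (an assumption; the protocol's own scale in Appendix 2 equates the two), all four fall in a row where the passages agree.
- On that assumption 0 of 18 reached Grade 2, with exact upper limit 1 − 0.025^(1/18) = 18.5%. A disputed case must also be judged unrelated, and no figure for that share is given.
- For infection, Section 2.3 reports no evidence of infection in the healthy-volunteer study. It gives no rate for patients with ulcerative colitis.

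The frequency is therefore not estimable from the documents. The weight of one case is: 1/12 = 8.3% of the planned active arm, or 1/6 = 16.7% of the placebo arm.

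**5. Which data are exposed.** Blood chemistry is scheduled on Days 2, 5 and 7 during treatment. A Day 2 result could decide whether the Day 5 profile is obtained, and a Day 5 result whether the Day 7 biopsy is taken on treatment. A Day 7 result would rarely matter for the biopsy, which is predose that day.

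**The case against.** The strongest reply is that the texts can be obeyed together. Section 4.1.3 lists events that are sufficient to stop dosing and does not say that they are the only ones. The instructions to continue treatment are in the Grade 1 rows of the tables. A site that applied the broader tables in every case would breach nothing. Section 7.1 is open-ended and also allows a stop on the investigator's or sponsor's judgement. Section 8 requires immediate safety concerns to be discussed with the sponsor to decide whether treatment goes on, and Section 4.1.4 makes the sponsor available at all hours.

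All of this stands, and it rules out some stronger readings that a reader might infer:

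- **That Section 4.1.3 requires dosing to continue for an unrelated elevation.** It omits a stop. It does not order continuation.
- **That SARS-CoV-2 is the only infection that stops dosing under Section 4.1.3.** It is the only one named, but the second bullet covers serious or severe, medically significant infections judged related.
- **That Section 7.1 excludes the tables.** An open list excludes nothing.
- **That about 12 × 4/18 = 2.7 active participants would be affected.** That counts mild rises, which are not in dispute if mild means Grade 1.

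The data consequence is also limited. The Early Withdrawal visit schedules a biopsy and PK samples as feasible, so stopping early puts the planned timing at risk but does not necessarily lose the tissue.

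What the reply does not do is say which text governs. Joint compliance is available only to an investigator who already takes the tables as binding. The tables are labelled guidelines, Section 4.1.3 is mandatory in tone, and its relatedness condition suggests that unrelated elevations were meant to be handled differently. Section 8 also allows no waivers, so sites need to know which rule they are held to.

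**Conclusion.** The point holds as an unresolved inconsistency in wording. The two sets of triggers differ for AST/ALT elevations of Grade 2 or higher judged unrelated, for non-serious Grade 2 infections other than SARS-CoV-2, and for unrelated Grade 3 or 4 infections other than SARS-CoV-2. They agree for related transaminase elevations, for SARS-CoV-2, and for severe, medically significant related infections.

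The number of participants affected cannot be estimated from the documents and may be zero. The matter is still worth correcting because it concerns mandatory stopping of an investigational drug for two risks the protocol itself names. The conclusion rests on the text alone and assumes that no site manual or other document outside those provided already settles precedence.

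**What to change.** The sponsor must reconcile Section 4.1.3 with Tables 5 and 6 so that one set of triggers is stated for transaminase elevation and one for infection, including whether relatedness is a condition. Which rule is clinically right is for the sponsor's medical lead; none is proposed here. Section 7.1 should then cite both Section 4.1.3 and Section 8.2.8.

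No new data collection is needed. Section 7.1 already requires the main reason for early treatment discontinuation in the eCRF, and that entry can record which criterion was met, at most with a sub-code. The count of adverse events leading to discontinuation would then rest on the same rule at every site.

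The cost is wording in Section 4.1.3 or Tables 5 and 6, a cross-reference in Section 7.1, and a note to sites. Sample size, visits and assays are unchanged. If the sponsor classes the change as substantial under Appendix 1, Section 2.3.1, it goes through ethics committee review and, where required, regulatory review before use.

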**4.1.4 Communication Strategy**

The Sponsor and Investigators will be in regular contact throughout the study by email/telephone/fax, as per normal interactions during the conduct of a clinical study. The Sponsor will arrange regular teleconferences and meetings to discuss study status.

The Sponsor will be available 24 hours per day to discuss any medical or study-related issues that may arise during the conduct of this study.

**4.2 SCIENTIFIC RATIONALE FOR STUDY DESIGN**

The study rationale is provided in Section 2.1.

**4.2.1 Rationale for Study Population**

Ulcerative colitis is a chronic disease. Despite the introduction of novel therapies and treatment strategies, many patients develop acute, severe episodes with high unmet medical need (Sedano et al. 2019). RO7486967 targets a new mechanism of action, which could be beneficial in the treatment of patients with UC (see also Section 2.1).

This study will recruit male and female participants who have active, moderate to severe

UC according to standard criteria and based on guidelines from Health Authorities.

UC patients presenting a mild renal impairment defined as creatinine clearance > 60 mL/minute are eligible to enter the study, supported by PBPK predictions: the impact on

systemic exposure is expected to be minimal, with an estimated increase of 10 % in the

AUC and no effect on Cmax.

**4.2.2 Rationale for Hospitalization**

PK behavior of RO7486967 in patients with UC is not known. In order to achieve a more optimized PK profile under controlled conditions, e.g., fasting conditions, participants will be hospitalized for the duration of the study.

**4.2.3 Rationale for Control Group**

RO7486967 will be compared against a placebo-concurrent control, with participants randomized in a 2:1 ratio to QD, oral administrations of RO7486967 or placebo, respectively. A placebo arm will be employed in order to derive a preliminary

assessment of the safety risk of RO7486967 in participants with UC and for equipoise in discriminating drug-relatedness of AEs. A placebo group will similarly inform the analysis of key biomarkers, including histopathologic changes in colonic biopsy samples and biomarkers used to establish PD effect.

**4.2.4 Rationale for Biomarker Assessments**

The main objectives of the mandatory biomarker strategy are to:

• Correlate drug exposure to rectal tissue target engagement (such as but not limited to caspase-1 cleavage) and downstream PD markers (such as, but not limited to, mature IL-1β, which may also be assessed in stool).

• Determine the impact of RO7486967 on inflammation markers (such as, but not limited to, C-reactive protein [CRP] in the blood and calprotectin in stool).

• Confirm and further investigate the level of inhibition of IL-1β production (through ex vivo cytokine release after LPS stimulation) in blood of patients.

Additional objectives include the assessment of changes in cellular composition (such as, but not limited to, neutrophils and inflammatory monocytes) and gene expression (such as, but not limited to, TNF, IL12B, CXCL10 inflammatory cytokines) upon RO7486967 treatment in rectal biopsies. Furthermore, the association of the microbiome composition (which may be assessed in stool or in the tissue) with PD and safety of RO7486967 will be explored. These data are of potential value for guidance in future patient stratification purposes or for treatment monitoring.

Serum and plasma samples will be collected to measure cytokines or other soluble biomarkers mechanistically linked to the mode of action of RO7486967. The impact of RO7486967 on these readouts will be explored.

In addition, safety exploratory biomarkers will be analyzed only in case signs of hepatotoxicity (such as transaminase increase) emerge during study.

Genotyping data may be used to explore whether the genotype may influence the target engagement or PD effects, or may affect the safety of RO7486967.

**4.3 JUSTIFICATION FOR DOSE**

The dose of 450 mg RO7486967 administered QD has been selected for this study based on PK, PD, and safety data from administration of single and multiple doses of RO7486967 in the completed SAD and MAD study in HVs. The dose of 450 mg was well tolerated when administered QD under fasted conditions for up to 7 consecutive days in study IZD334-001. This dose produced a robust PD effect by reducing the production of IL-1β in ex vivo LPS/nigericin stimulated whole blood by 99% up to 10 hours postdose and 90% over the dosing interval (24 hours), as compared with those of baseline. Therefore, this dose level was chosen for Study BP43099, as it is expected that it will provide a detectable PD readout also at the gut tissue level.

Further details are provided in the IB.

**4.4 END OF STUDY DEFINITION**

A participant is considered to have completed the study when the last scheduled procedure shown in the schedule of assessments has been completed.

The end of the study is defined as the date when the last participant last visit (LPLV) occurs. LPLV is expected to occur approximately 2 weeks after the last participant is randomized.

**5. STUDY POPULATION**

The study population rationale is provided in Section 4.2.1.

Participants of this study are male and female patients of 18 to 75 years of age

(inclusive), with active, moderate to severe UC.

**5.1 INCLUSION CRITERIA**

Participants are eligible to be included in the study only if all of the following criteria apply.

**Informed Consent**

1. Able and willing to provide written informed consent and to comply with the study protocol according to International Conference on Harmonisation (ICH) and local regulations. A signed Informed Consent Form must be available from the participant

before starting any study-specific assessments.

**Age**

2. Between 18 to 75 years of age (inclusive), at the time of signing the informed consent.

**Type of Participants and Disease Characteristics**

3. Diagnosis of UC at least 12 weeks prior to screening.

4. Patients with active moderate to severe UC as measured by partial MCS ≥ 3 and ≤

8, with stool frequency subscore ≥ 1, rectal bleeding subscore ≥ 1, and fecal calprotectin ≥ 150 μg/g.

5. Most recent colonoscopy within the preceding 3 years at the time of screening.

6. Screening colonoscopy for colorectal cancer conducted within the prior two years if:

• History of pancolitis and disease duration ≥ 8 years, or

• History of left-sided colitis and disease duration ≥ 12 years.

**Weight**

7. Body mass index (BMI) within the range of 18-35 kg/m2 (inclusive).

**Sex and Contraceptive/Barrier Replacement**

8. Male and female participants

The reliability of sexual abstinence for female enrollment eligibility needs to be evaluated in relation to the duration of the clinical study and the preferred and usual lifestyle of the participant. Periodic abstinence (e.g., calendar, ovulation, symptothermal, or post-ovulation methods) and withdrawal are not acceptable methods of preventing drug exposure.

a) Female participants

A female participant is eligible to participate if she is not pregnant, not breastfeeding, and at least one of the following conditions applies:

• Women of non-childbearing potential (WONCBP—i.e., post-menopausal;

pre-menarchal; or pre-menopausal with documented hysterectomy, bilateral salpingectomy, or bilateral oophorectomy).

• WOCBP (a woman is considered fertile following menarche and until becoming post-menopausal unless permanently sterile), who:

o Agree to remain abstinent (refrain from heterosexual intercourse) or use at least 1 acceptable contraceptive methods (see Appendix 5) for at least

1 month before dosing, during the treatment period and for at least 7 days after the final dose of RO7486967/placebo.

The following are acceptable contraceptive methods: bilateral tubal occlusion, male sterilization, established proper use of hormonal contraceptives that inhibit ovulation, hormone-releasing intrauterine devices and copper intrauterine devices, male or female condom with or without spermicide; and cap, diaphragm, or sponge with spermicide (see Appendix 5).

b) Male participants

No contraceptive requirements for male participants.

**5.2 EXCLUSION CRITERIA**

Participants are excluded from the study if any of the following criteria apply:

**Medical Conditions**

1. Diagnosis of fulminant UC, Crohn’s disease*,* indeterminate colitis, microscopic colitis, segmental colitis associated with diverticulosis, ischemic colitis, or radiation- induced colitis based on medical history, endoscopy, and/or histological findings.

2. Active infections requiring systemic therapy with antibiotic, antiviral, or antifungal medication or febrile illness within 7 days before Day −1.

3. History of primary or acquired immunodeficiency.

4. History of chronic pulmonary disease with resultant clinically significant abnormal pulmonary function.

5. History of clinically significant cardiac or cardiovascular disease or uncontrolled hypertension.

6. Presence of chronic liver disease.

7. Evidence of colonic dysplasia that cannot be completely removed.

8. Women: Pregnant or lactating.

9. Any condition or disease detected during the medical interview/physical examination that would render the patient unsuitable for the study, place the patient at undue

risk, or interfere with the ability of the patient to complete the study in the opinion of

the Investigator.

10. History of tuberculosis or a positive Quantiferon® Gold test.

11. History of clinically significant severe drug allergies, multiple drug allergies, or allergy to any constituent of the investigational medicinal product (IMP).

12. Lymphoma, leukemia, or any malignancy within the past 10 years, except for basal cell or squamous epithelial carcinomas of the skin that have been resected with no evidence of metastatic disease for 3 years and in situ carcinoma of the cervix that was completely removed surgically.

13. History or presence of clinically significant ECG abnormalities before study drug administration (e.g., PQ/PR interval ≥ 220 ms, QT corrected for heart rate using Fridericia’s correction factor (QTcF), < 350 or ≥ 450 ms) or clinically significant cardiovascular disease (e.g., cardiac insufficiency, coronary artery disease, cardiomyopathy, congestive heart failure, family history of congenital long QT interval syndrome, family history of sudden death).

14. Fecal microbiota transplant, defined as receipt of any product derived from the feces of another human and administered per oral, per nasogastric or nasoduodenal, or per rectum within the last 6 months.

15. Bowel surgery within 12 months prior to study start.

16. History of colectomy or partial colectomy.

17. History of known bleeding disorder or diseases with an increased risk of bleeding tendency.

